#### Enhanced treatment-as-usual (ETAU)

Participants in the ETAU arm will be emailed a resource package comprising handouts detailing the strategies taught in PM+, with instructions to work through in a self-paced manner across the course of a six-week duration. Those randomized to the ETAU arm will not receive support from a clinical psychologist/group facilitator.

### Screening measure

The General Health Questionnaire (GHQ-12) is a well validated indicator of psychological distress [15] that will be used to screen individuals eligible to partake in the trial (see Table 1). The GHQ-12 comprises of 12 questions about general wellbeing, experience of depressive and anxiety symptoms, and sleep disturbances over “the past few weeks”. Items are scored on a 4-point scale (range 0 to 12; higher scores indicate severe psychological distress), where a cutoff of 3 (using the 4-point, 0–0–1-1, original dichotomous scoring system) will be used to screen individuals with psychological distress in relation to COVID-19 [16].

**Table 1 Tab1:** Overview of measures administered at assessment time points

Construct	Pre-assessment	Post-treatment	2-months post-treatment^a^	6-months post treatment
Screener				
1. Psychological distress	GHQ-12			
Primary Outcome				
2. Anxiety and depression	HADS	HADS	HADS	HADS
Secondary Outcomes				
3. Generalised anxiety	GAD-7	GAD-7	GAD-7	GAD-7
4. Sleep Impairment	SII	SII	SII	SII
5. Mood	PANAS	PANAS	PANAS	PANAS
6. COVID stress	CSS	CSS	CSS	CSS
7. Anhedonia	Pleasure Scale	Pleasure Scale	Pleasure Scale	Pleasure Scale

Note. ^a^ = Primary outcome time point. *HADS* Hospital Anxiety and Depression Scale, *GAD-7* Generalized Anxiety Disorder-7, *SII* Sleep Impairment Index, *PANAS* Positive and Negative Mood Scale, *CSS* COVID-19 Stress Scale

### Primary outcome

The primary outcome will be severity of anxiety and depressive symptoms as measured using the Hospital Anxiety and Depression Scales (HADS [17]). The HADS is a 14-item scale consisting of two sub-scales: HADS-A (Anxiety, 7 items, range 0–21) and HADS-D (Depression, 7 items, range 0–21). Higher scores indicate more severe anxiety and/or depression. The minimal clinically important difference has been determined at 1.32 for HADS-A and 1.40 for HADS-D [18].

### Secondary outcomes

Worry will be assessed using the Generalized Anxiety Disorder Scale (GAD-7 [19]). This scale has demonstrated good reliability, and validity and is useful in assessing the presence and severity of generalized anxiety, where higher scores indicate more severe symptoms. High levels of sensitivity (89%) and specificity (82%) relative to generalized anxiety disorder have been demonstrated using this scale [20].

Sleep difficulties will be assessed using the Insomnia Severity Index (ISI [21]). The ISI is a 7-item measure of sleep impairment; this study used 5 of the 7 items because of time constraints within a larger clinical interview. The items indexed impairment in sleep onset, maintenance, early waking, disturbance caused by sleep problems, and distress caused by sleep problems (this version will omit items indexing satisfaction with sleep and the extent to which sleep problems were noticeable by others). The internal consistency of the 5-item version is 0.87, and the item-total correlations varied from 0.46 (waking early) to 1.00 (delayed onset sleep), with a mean correlation of 0.57. These values are similar to the values reported for the 7-item measures [22], and validate our use of the 5-item scale. Each item is rated on 5-point rating scale (0–4) providing a potential total score of 28, and the recommended cut-off for identifying insomnia is a score of 12. Accordingly, in recognition that we used 5 of the 7 items, we adopted a pro-rated score of 12 as a conservative index of sleep disturbance.

Mood will be assessed using the Positive and Negative Affect Schedule (PANAS [23]) to provide brief measure of positive- and negative affect (two 10-item mood scales). Respondents are asked to rate the extent to which they have experienced a particular emotion “right now” to capture a present-moment timeframe. Items on this scale broadly capture the affective lexicon and has demonstrated high internal consistency and good convergent and discriminant validity [23].

Anhedonia will be with the Pleasure Scale which asks participants to respond to 36 questions about their capacity to experience pleasure in various situations [24]. Each item is scored on a 5-point scale (range 36–180, with lower scores indicating more severe anhedonia). The scale has strong internal reliability and identifies depressed individuals with extreme anhedonia [24].

COVID-19 related concerns will be assessed using the COVID Stress Scales (CSS) that has been developed to index the extent to which an individual engages in worry about COVID-19 related issues [25]. This scale comprises six domains including (1) fears about the dangers of COVID-19, (2) fears about economic consequences of COVID-19, (3) COVID-19related xenophobia, (4) fear of COVID-19 contamination, (5) traumatic stress symptoms, and (6) excessive checking and reassurance seeking. This was used in the current study to assess specific pandemic related emotional reactions and has evidenced good reliability and internal consistency [25]. Each item is scored on a 5-point scale (range 0–24 on each subscale, with higher scores indicating more severe problems).

### Data management

Adverse events will be monitored at each assessment. Any adverse events that occur during the trial involving untoward medical or psychological occurrence in a participant that is related to the trial will be reported in the study on a standard form and submitted to the study’s Data Monitoring Committee and Trial Sponsor. These adverse reactions will be referred to appropriate services and the relevant psychologist managing this case will follow up at 1 month.

As this is a treatment trial, participants will be required to have their identities known to the study because they are seen on a weekly basis, and then be contacted for follow-up assessment. All data entered by participants during the online surveys collected at pretreatment, posttreament, and follow-up will be entered on an electronic database in a deidentified manner in which participants are allocated a unique identification number. Access will be restricted to research staff directly involved in the study. If the data is moved to any other computer location it will have AES-256 bit encryption. We routinely audio record group therapy sessions in line with CONSORT requirements for subsequent testing of treatment fidelity via independent coding of experts. The research staff working on the project will initially have access to the data via the UNSW Research Long Term Data Store Interface.

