## Methods

### Aim and design

This study aims to evaluate the effectiveness of an adapted version of PM+ to specifically target COVID-19 related distress in reducing anxiety and depression. We will conduct a two-arm single-blind, parallel, randomized controlled trial (RCT) comparing PM+ with enhanced treatment as usual (ETAU) in 240 participants (see Fig. 1 for an overview of the design, following the Standard Protocol Items: Recommendations for Intervention Trials (SPIRIT [14];). This trial adhered to the trial protocol (version 2, April 10, 2020). The study design will employ a 2 (Treatment Condition) × 4 (Assessment Point) factorial design. Participants will be assessed at baseline, post-intervention, and two- and six-month follow-ups. The primary outcome time point is the two-month assessment, and the primary outcome is anxiety and depression. Secondary outcomes include worry, sleep impairment, positive and negative mood, anhedonia, and COVID-19-related concerns.

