### Participants

articipant inclusion criteria are a) adult (18 years or older); b) score ≥ 3 on the General Health Questionnaire-12; GHQ-12 [15]); and (c) report sufficient English language comprehension. Exclusion criteria are: a) current psychosis; b) imminent suicidal risk; c) current substance dependence (but not abuse); or d) no internet-based access for teleconferencing.

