### Interventions

#### Problem management plus (PM+)

The WHO PM+ programme is a brief psychological intervention that seeks to reduce symptoms of stress (e.g. depression, anxiety) for those affected by ongoing adversity. This program was adapted to include evidence-based strategies that specifically target COVID-19 related distress. This includes education about common reactions to COVID-19, stress management, structured problem solving, worry management, behavioural activation and skills to strengthen access to social support. Finally, relapse prevention will involve teaching participants relapse prevention techniques, including identification of possible future relapse situations and rehearsal of strategies to manage these situations. PM+ content was adapted to expand its content to address excessive worries because the nature of the pandemic is that distress can be heightened by worries about health of self and others, employment security, and financial stress, as well adapting the content to manage loss of normal activities during lockdowns and limited access to use social supports. This adapted version of PM+ is delivered over 6 weekly sessions of 60-min duration. In this RCT, PM+ will be delivered in anticipated group size of 3–4 participants via a videoconferencing platform. PM+ group facilitators will be Masters or Doctoral trained clinical psychologists.

Adherence to PM+ protocol will be ensured by weekly group supervisions including the group facilitators and supervisors. To evaluate treatment fidelity, treatment sessions will be audiotaped and 10% of all PM+ sessions will be independently rated for adherence by two independent clinical psychologists. Raters will be required to nominate what therapy components were present in each session and the quality with which these components were administered.

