### Analysis

A total of 240 participants will be included in the trial. Power calculations were based on previous trials of group-based PM+ [13], and indicated a minimum sample size of 105 participants per group is needed to provide power of 0.95 (alpha = 0.05, two-sided) to achieve an effect size of 0.5 between condition; allowing for attrition of 10% at follow-up, this study aimed to recruit 240 participants. An intent-to-treat analysis using Hierarchical Linear Mixed Modelling will be used to assess differential effects of each condition. This statistical method effectively handles missing data by calculating estimates of trajectories. For the posttreatment analyses between the two conditions, analyses will focus on linear time effects, treatment conditions, and interactions. Fixed effects parameters will be tested with the Wald test (t-test, *p* < .05, two-sided) and 95% confidence intervals. Cohen’s (d) effect size will be calculated for all analyses. The primary outcome measure will be the HADS. The primary outcome timepoint will be the 2 months assessment. Given the speed of this trial, there will be no interim analyses to determine if the trial needs to be terminated prematurely.

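### The reporting rule describes the form to the Data Monitoring Committee for trial-related adverse events and gives other events, including serious and suicidality events, no stated route to the committee

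*Protocol article*

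**What the plan says.** The Data management section of the protocol article opens its safety paragraph without any limit on cause: "Adverse events will be monitored at each assessment". The next sentence covers reporting. It describes events "involving untoward medical or psychological occurrence in a participant that is related to the trial will be reported in the study", and these go "on a standard form and submitted to the study’s Data Monitoring Committee and Trial Sponsor". The sentence after that gives the same events a causal name: "These adverse reactions will be referred to appropriate services", with follow-up at one month by the psychologist managing the case.

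Four other places bear on the point:

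- **Aim and design:** both arms share one schedule. "Participants will be assessed at baseline, post-intervention, and two- and six-month follow-ups".
- **Participants:** entry requires a GHQ-12 score of 3 or more. "Exclusion criteria are: a) current psychosis; b) imminent suicidal risk" shows that acute risk is screened out at entry.
- **Problem management plus (PM+):** to explain why the content was adapted, the article says that "the nature of the pandemic is that distress can be heightened by worries about health of self and others, employment security, and financial stress".
- **Analysis:** "there will be no interim analyses to determine if the trial needs to be terminated prematurely".

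**The concern.** Monitoring is unrestricted, but the described route to the committee begins with a judgement that the event is related to the trial. Participants are selected for distress, and the exclusion for imminent suicidal risk is an entry criterion. New risk during six weeks of intervention and six months of follow-up is therefore foreseeable. Some worsening will have plausible causes outside the trial, so relatedness will often be hard to settle for an individual.

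Randomisation offers a comparison that needs no such judgement: all events, counted by arm, at assessments common to both arms. If the form is used as described, the committee would not necessarily receive that comparison. At stake is whether it would learn in time of serious events or emerging suicidal risk that someone had put down to outside causes. The efficacy result is not at stake.

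**Working it through.** This is a reporting rule. The article gives no adverse event rate, no expected share of events judged related and no planned between-arm safety test, so no arithmetic applies. The check is a reading of the text.

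1. **What is monitored.** Adverse events at each assessment, with no relatedness condition (Data management, first sentence).

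2. **What goes on the form.** The sentence describing the form carries the condition that the occurrence is related to the trial. The condition is unlikely to be loose wording, because the following sentence calls the same events adverse reactions, a term that implies a cause.

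3. **Whether another route exists.** No other section sends anything to the committee. The Analysis section rules out interim analyses for early termination. Nothing in the article says that outcome scores, serious events of any cause or suicidality events are passed to the committee during the trial.

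4. **Who judges relatedness.** The article does not say, nor whether the judgement is blind to arm. Nothing in it counters a wrong attribution in a single case.

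5. **What is captured without a causality judgement.** Table 1 lists the HADS, GAD-7, a sleep measure, the PANAS, the COVID stress scale and the Pleasure Scale at all four time points. The Analysis section specifies an intention-to-treat mixed model by condition. Worsening on these scales is therefore recorded by arm, whatever its cause, and can be seen in the final analysis.

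6. **What steps 1 to 5 leave over.** Two things: timing, since the scale scores are not described as reaching the committee while the trial runs; and content, since none of the listed outcome measures is described as covering suicidal risk, and serious events are not scale scores. The gap that remains is oversight during the trial, mainly of serious and suicidality events.

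**The case against.** The strongest reply is that the restriction is partly inferred. The article says that trial-related events will be reported; it does not say that others will not be. It is a condensed article that refers to a full trial protocol (version 2, April 10, 2020), which is not at hand. Procedures for serious events and the committee's remit commonly sit in such a protocol or in a charter, and their absence here is no fault. This stands as far as it goes: the point cannot be that a serious-event procedure is missing. What remains is that the article does state a rule, and that rule makes relatedness the condition for the form.

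The second reply is that symptom deterioration is already measured by arm. That also stands, and it narrows the point to oversight during the trial.

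The third is that the list of pandemic worries explains the adaptation of the content and says nothing about how events are attributed. That is correct. It shows only that the article recognises outside causes of distress.

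A reader might infer several stronger things that the article does not support:

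- **That unrelated events are discarded.** The rule concerns reporting and forwarding. Nothing says they are dropped from the trial's records.
- **That attribution differs between arms.** Enhanced usual care has no facilitator, so this is possible, but nothing shows it.
- **That the loss can be expressed as lost power to detect harm.** Any such figure would rest wholly on assumed event rates, assumed shares judged related and a safety test that the article does not plan. If relatedness were judged accurately, the loss could be nil.

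**Conclusion.** The point holds in a limited form. As written, the article conditions the form to the committee and sponsor on relatedness to the trial and describes no route for other events, so a causality judgement could keep a serious or suicidality event from the committee during the trial. This assumes that the described rule is followed literally and that the full protocol adds no separate route; the documents at hand cannot settle the second.

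The size cannot be stated from the article. This is a minor safety-oversight item, a cheap improvement to consider. It does not affect the HADS comparison at two months or its interpretation.

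**What to change.** Reword the reporting sentence in Data management so that all adverse events found at the common assessments, and at minimum all serious and suicidality events, go on the standard form and to the Data Monitoring Committee, tabulated by arm, whatever their relatedness. Make relatedness a separate field on that form, judged by someone blind to arm where possible. If the full protocol already does this, bring the article's sentence into line with it.

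The cost is one reworded rule, one added field, and somewhat more logging and review in a trial of 240 participants. The outcomes, assessment schedule, sample size and primary analysis do not change.

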### Analysis

A total of 240 participants will be included in the trial. Power calculations were based on previous trials of group-based PM+ [13], and indicated a minimum sample size of 105 participants per group is needed to provide power of 0.95 (alpha = 0.05, two-sided) to achieve an effect size of 0.5 between condition; allowing for attrition of 10% at follow-up, this study aimed to recruit 240 participants. An intent-to-treat analysis using Hierarchical Linear Mixed Modelling will be used to assess differential effects of each condition. This statistical method effectively handles missing data by calculating estimates of trajectories. For the posttreatment analyses between the two conditions, analyses will focus on linear time effects, treatment conditions, and interactions. Fixed effects parameters will be tested with the Wald test (t-test, *p* < .05, two-sided) and 95% confidence intervals. Cohen’s (d) effect size will be calculated for all analyses. The primary outcome measure will be the HADS. The primary outcome timepoint will be the 2 months assessment. Given the speed of this trial, there will be no interim analyses to determine if the trial needs to be terminated prematurely.

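### The analysis names linear time, condition and interactions, but no stated parameter is the between-arm HADS difference at the primary 2-month assessment

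*Protocol article*

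**What the plan says.** The Analysis section of the protocol article fixes the endpoint: "The primary outcome measure will be the HADS", and "The primary outcome timepoint will be the 2 months assessment". Table 1 marks the same timepoint as primary.

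The Aim and design section gives the schedule ("Participants will be assessed at baseline, post-intervention, and two- and six-month follow-ups") and treats time as a factor with four levels: "The study design will employ a 2 (Treatment Condition) × 4 (Assessment Point) factorial design".

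For the model, the Analysis section says "An intent-to-treat analysis using Hierarchical Linear Mixed Modelling will be used to assess differential effects of each condition", then "For the posttreatment analyses between the two conditions, analyses will focus on linear time effects, treatment conditions, and interactions", and then "Fixed effects parameters will be tested with the Wald test". The same section sizes the trial at 105 per group for power 0.95, two-sided alpha 0.05 and a between-condition effect size of 0.5, raised to 240 in total for 10% attrition.

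No sentence says which model parameter or contrast answers the 2-month question.

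**The concern.** With linear time coded from baseline, the condition term is the fitted gap at baseline and the interaction is the difference in slopes. Neither is the HADS difference at 2 months. The article therefore states three things that do not fit together: a single-timepoint endpoint, a four-level assessment factor, and a straight line in time.

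An unseen analysis plan might settle which contrast is reported. But linear time is a choice the article itself states, and that choice conflicts with the endpoint it declares.

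Two things are at stake. If the interaction is reported as the primary result, its power and its meaning depend on the shape of the effect over time, and the 6-month visit has the most leverage. And while the primary parameter is unnamed, a slope result and a 2-month result both remain available after the data are seen.

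**Working it through.** **The plan's own figure.** For two independent means with d = 0.5, two-sided alpha 0.05 and power 0.95, the normal approximation gives n = 2(1.960 + 1.645)²/0.5² ≈ 104 per group. The noncentral t gives power 0.9483 at 104 and 0.9501 at 105. So 105 reproduces, as a comparison of two means at one timepoint. Then 105/0.9 = 116.7, and 120 per arm covers it.

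**Inputs.** From the article: 105 per arm, d = 0.5, four visits, and a six-week treatment ("This adapted version of PM+ is delivered over 6 weekly sessions of 60-min duration"). Assumed, because the article gives none: SD 1, equal correlation r = 0.5 between visits, visits at months 0, 1.5, 3.5 and 7.5 (six weeks of treatment, then 2 and 6 months), complete data, and the effect profiles below. Profiles list the true between-arm difference in SD units, benefit positive, at baseline / post-treatment / 2 months / 6 months.

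**Formulas** (d̄ is the mean of the visit differences, t₂ the 2-month visit time, S = Σ(t − t̄)², K visits):
- Slope difference: b = Σ(t − t̄)d / S, with SE = √[2(1 − r)/(nS)].
- Fitted 2-month difference: d̄ + b(t₂ − t̄), with SE = √{(2/n)[(1 + (K − 1)r)/K + (1 − r)(t₂ − t̄)²/S]}.
- Direct 2-month contrast: SE = √[4(1 − r)/n] for change scores, or √[2(1 − r²)/n] adjusted for baseline.

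**Direct contrast at 0.5 SD.** Change score: SE = √(2/105) = 0.138, z = 3.62, power 0.95. Baseline-adjusted: SE = √(1.5/105) = 0.120, z = 4.18, power 0.99.

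**All four visits, months.** t̄ = 3.125; S = 9.766 + 2.641 + 0.141 + 19.141 = 31.69. SE(b) = √[1/(105 × 31.69)] = 0.0173. SE of the fitted 2-month difference = 0.109.
- Sustained, 0/0.5/0.5/0.5: b = 0.5(−1.625 + 0.375 + 4.375)/31.69 = 0.0493; z = 2.84; interaction power 0.81. Fitted 2-month difference = 0.375 + 0.0493 × 0.375 = 0.39, against a true 0.50; its own test has power 0.95.
- Fading, 0/0.5/0.5/0.2: b = 0.0079; z = 0.46; interaction power 0.07. Fitted 2-month difference 0.30; its own test has power 0.79.
- 6 months only, 0/0/0/0.6: b = 0.6 × 4.375/31.69 = 0.0828; z = 4.78; the interaction is significant with probability above 0.98, although the true 2-month difference is zero.

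**All four visits, coded 0–3.** S = 5; SE(b) = √[1/(105 × 5)] = 0.0436.
- Sustained: b = 0.15; z = 3.44; interaction power 0.93; fitted difference 0.45, with power 0.98.
- Fading: b = 0.06; z = 1.37; interaction power 0.28; fitted difference 0.33, with power 0.84.
- 6 months only: b = 0.18; z = 4.12; interaction significant with probability 0.98.

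**Baseline, post-treatment and 2 months only, 0/0.5/0.5.**
- Months 0/1.5/3.5: t̄ = 1.667, S = 6.167, b = 0.135; interaction power 0.93. Fitted 2-month difference = 0.333 + 0.135 × 1.833 = 0.58.
- Coded 0–2: b = 0.25, which is half the baseline-to-2-month difference in change, so its test is the direct change-score contrast, power 0.95. Fitted difference = 0.333 + 0.25 = 0.58.

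The fading and 6-month-only problems do not arise here, because both come from the 6-month visit.

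**Baseline to post-treatment only.** With two visits a linear term fits the means exactly and does no harm, but the sentence then gives no model for the 2-month endpoint.

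**Sensitivity to r.** With 108 per arm (120 × 0.9), four visits in months and r from 0.3 to 0.7, interaction power for a sustained 0.5 SD effect runs from 0.68 to 0.96.

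**The case against.** The opposing case is substantial. The sentence is limited to posttreatment analyses, and nothing says that one line is fitted through all four visits for the primary test. The Procedure section mentions repeating the battery only at post-treatment and 2 months, which supports a three-visit reading (Table 1 and the Aim and design section do include 6 months). On that reading the loss of power is small. The model also lists condition as a term, so with time centred at 2 months it could yield a 2-month estimate whose test keeps power of 0.79 to 0.98 in the sustained and fading profiles. Every profile, spacing and correlation is assumed. Covariance structure and similar details belong in an analysis plan.

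All of that stands, and it limits the point. A reader might infer that the confirmatory test is shown to be of the wrong hypothesis, or that the trial will lose nearly all its power or produce a false positive. The documents do not support this: the article does not say that the interaction alone is the primary test, and the severe figures need both a four-visit line and particular effect shapes.

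The objection does not remove the mismatch. Centring at 2 months is nowhere stated, and a 2-month value read off a line is unbiased only if the between-arm gap is linear in time. The four-level design in the Aim and design section is not carried into the Analysis section.

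**Conclusion.** The concern holds in a limited form. The article states linear-time terms, declares a single-timepoint primary endpoint, and powers the trial for a comparison of means at one timepoint, without tying the endpoint to any parameter. The consequence depends on the reading:

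- **Four visits:** the fitted 2-month difference is biased unless the gap is linear in time. Interaction power ranges from good to almost none according to effect shape and time coding, and the interaction can be significant with no 2-month effect.
- **Three visits:** little power is lost for a sustained effect, but the 2-month difference is overstated at about 0.58 instead of 0.50.
- **Two visits:** the linear term is harmless, and the primary timepoint has no stated model.

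The figures show direction and possible size under assumed inputs; they do not predict this trial's result. The mismatch itself rests only on the text.

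**What to change.** Replace the sentence on linear time with wording such as: Assessment is a four-level categorical factor; the model contains condition, assessment and condition × assessment, adjusted for baseline HADS; the primary test is the PM+ minus ETAU contrast in HADS at the 2-month assessment; the post-treatment and 6-month contrasts are secondary.

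This agrees with the 2 × 4 design and with the comparison behind the sample size. It costs a few more model parameters and needs no new data or participants. The covariance structure, and whether baseline enters as a covariate or through equal baseline means, can be left to the analysis plan.

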### Procedure

Following receipt of consent, participants will be directed to a webpage that that will include the General Health Questionnaire (GHQ). If participants score ≥ 3 on the GHQ they will be randomized to either PM+ or ETAU. If participants are not selected because they score below the cut-offs for the GHQ-12, they will be provided feedback on their test outcomes and reasons why they are not eligible for the study will be explained to them. If participants meet any of the exclusion criteria, participants will be referred to seek support from their local physician for further management with specialised services. Participants will then be directed to an online assessment batter, which will include the Hospital Anxiety and Depression Scales (HADS), Generalized Anxiety Disorder Scale (GAD-7), Sleep Impairment Index (SII), and Positive and Negative Affect Schedule (PANAS), Pleasure Scale (PS), Coronavirus Stress Scale (CSS). This online assessment, which will be repeated at post-treatment and 2-month follow-up will ensure independent assessments because no research personnel will administer these. Participants were reimbursed $50 if they completed all assessments.

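### The described HADS model leaves the arms free to differ at baseline and names no baseline adjustment, which gives up precision that data already collected could supply

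*Protocol article*

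**What the plan says.** The Analysis section of the protocol article plans an intent-to-treat hierarchical linear mixed model. In a sentence introduced as covering the post-treatment comparison it states that "analyses will focus on linear time effects, treatment conditions, and interactions". It describes no other model for the two-month assessment, which is the primary time point. The section names neither a covariate nor a constraint on the baseline means.

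Under Aim and design: "The study design will employ a 2 (Treatment Condition) × 4 (Assessment Point) factorial design". The four points are baseline, post-intervention, two months and six months, and Table 1 lists HADS at all four.

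The sample-size text "indicated a minimum sample size of 105 participants per group is needed to provide power of 0.95" at two-sided alpha 0.05, and the effect size is given as the one "to achieve an effect size of 0.5 between condition". The article gives neither the SD behind that effect size nor any correlation between assessments.

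The Procedure section says: "If participants score ≥ 3 on the GHQ they will be randomized to either PM+ or ETAU". The online battery containing HADS is described after that step. Table 1 lists GHQ-12 only as the screener, and the Analysis section gives it no role.

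**The concern.** With baseline as an outcome occasion and a condition main effect in the model, the model estimates a baseline difference between arms. Randomisation makes that difference zero in expectation if baseline precedes allocation. The treatment effect then rests on the interaction, that is, on differences in change. Such a contrast carries the full sampling noise of the baseline score. Treating the baseline mean as common to both arms, or conditioning on the baseline score, removes part of that noise using data the trial collects anyway.

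At stake is precision on the primary outcome and, in the same way, on every secondary scale. If r is modest, the free-baseline contrast can even be less precise than the plain comparison of follow-up scores. Six weekly sessions plus two months put the primary assessment about 3.5 months after baseline, so a modest r cannot be excluded, but the article offers no evidence on it either way.

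**Working it through.** **Inputs from the Analysis section.** Effect size 0.5, two-sided alpha 0.05, power 0.95, 105 per group, 10% attrition, 240 recruited.

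**Assumptions.** The correlation r between baseline and two-month HADS is not documented, so a range is shown. Equal SDs are assumed at both occasions, and d = 0.5 is taken in raw-score SD units except where noted.

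**The plan's own figure.** The normal approximation gives n = 2(1.960 + 1.645)²/0.5² = 104 per group. The noncentral t gives power 0.9501 at 105, so the stated 105 reproduces. For attrition, 210/0.9 = 233.3, so 234 are needed. Recruiting 240 covers this and leaves 240 × 0.9/2 = 108 per arm.

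**Two-month contrast, categorical time.** Relative to a plain comparison of follow-up scores, the variance factor is:

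- free-baseline change contrast: f = 2(1 − r)
- baseline-adjusted contrast: f = 1 − r²
- ratio of the two: 2(1 − r)/(1 − r²) = 2/(1 + r), which exceeds 1 for every r below 1

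Power with 108 per arm is Φ(0.5/√(2f/108) − 1.96):

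| r | f, change | f, adjusted | ratio | power, change | power, adjusted |
|---|---|---|---|---|---|
| 0.2 | 1.60 | 0.96 | 1.67 | 0.828 | 0.963 |
| 0.3 | 1.40 | 0.91 | 1.54 | 0.874 | 0.971 |
| 0.4 | 1.20 | 0.84 | 1.43 | 0.918 | 0.980 |
| 0.5 | 1.00 | 0.75 | 1.33 | 0.957 | 0.989 |
| 0.6 | 0.80 | 0.64 | 1.25 | 0.984 | 0.996 |
| 0.7 | 0.60 | 0.51 | 1.18 | 0.997 | 0.999 |

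With exactly 105 per arm and the noncentral t, the change contrast has power 0.862, 0.909, 0.950 and 0.981 at r = 0.3, 0.4, 0.5 and 0.6; the adjusted contrast has 0.966, 0.976, 0.986 and 0.995. By the normal approximation, the change contrast reaches 0.95 at r of about 0.48 with 108 per arm and 0.495 with 105.

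**The model as worded, with linear time.** The interaction is now a slope difference over all four visits, so the factors above do not apply directly. Generalised least squares was used with assumed visit times of 0, 1.5, 3.5 and 7.5 months, compound symmetry, r = 0.3 and 108 per arm. The standard error of the fitted two-month difference is 0.071 with a free baseline and 0.059 with a common one, a variance ratio of (0.071/0.059)² ≈ 1.45.

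- Arm difference growing linearly to 0.5 at two months: power above 0.99 with either baseline handling.
- Arm difference of 0.5 appearing post-treatment and staying constant: power 0.684 (free) and 0.989 (common). The fitted two-month difference is only 0.17 and 0.25, because a straight line does not fit. This gap therefore mixes precision with misfit.

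**The case against.** The strongest objection is that this is one summarising sentence in a journal article. It says where the analyses will focus, and it excludes neither a covariate nor a common baseline mean. Such detail often sits in a full protocol or SAP, which is not shown. This stands to the extent that one cannot say the trial will adjust for nothing, only that no adjustment is named. What remains is that the article does name the fixed effects and does make baseline an outcome occasion. Read as written, that is a free-baseline model, and a better one is available.

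A reader might infer that the trial misses its stated power. The documents do not support that. A shortfall needs both an undocumented r below about 0.49 and an effect size in raw-score SD units. If d = 0.5 is in change-score SD units, 105 per arm gives 0.95 at any r. Nor can one say that 105 fits only a comparison of follow-up scores: a change contrast at r = 0.5 gives the same 0.950.

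A reader might also call the planned effect a change-from-baseline contrast. That is exact only with categorical time or two visits. Under linear time it is a slope difference, and its power can depend more on the shape of the trajectory than on baseline handling.

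Two further points stand. The benefit of GHQ-12 cannot be quantified: no GHQ–HADS correlation is given, and the entry cut-off narrows its range. And the baseline HADS remedy presupposes measurement before allocation, which the Procedure section does not secure.

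**Conclusion.** The point holds as one of efficiency and clarity. The model as described lets the arms differ at baseline and names no baseline adjustment. If baseline HADS precedes allocation, the free-baseline contrast is unbiased with valid type I error, but its variance at two months under categorical time is 2/(1+r) times that of the adjusted contrast, or 1.54 to 1.18 for r from 0.3 to 0.7. The existence of the loss does not depend on r; only its size does. Under linear time a common baseline also reduces variance, by a similar order in the one configuration checked.

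The sample-size figure is not in error. An adjusted analysis would meet 0.95 throughout r = 0.2 to 0.7, whereas the free-baseline change contrast does so only from about 0.49 upward when d is in raw-score SD units.

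If HADS is in fact completed after participants know their allocation, neither the change contrast nor baseline adjustment is safe. The order of these steps therefore has to be settled first.

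**What to change.** 1. Confirm in the Procedure section, or set, that the baseline HADS battery is completed before allocation.
2. Once that is settled, for HADS and each secondary scale, estimate the two-month arm difference from a mixed model with a common baseline mean in both arms, or with the baseline score as a covariate and only post-baseline occasions as outcomes. State the two-month contrast explicitly.
3. Add the GHQ-12 score as a prespecified covariate. It is collected before randomisation, so it can be used as the procedure stands.

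Items 2 and 3 cost a sentence or two in the Analysis section or SAP and need no new data. Item 1 costs one clarifying sentence if the battery already precedes allocation. If it does not, the order of the online steps has to change, and for participants already enrolled in the old order the baseline HADS adjustment should not be assumed safe.
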